#### Statistical analysis

Differences in baseline characteristics (i.e., intrinsic and injury-related variables) between both intervention groups will be assessed using the Student’ s *t* test (parametric continuous data), the Mann-Whitney *U* test (nonparametric continuous data) or the chi-square test (categorical data).

Unadjusted analysis by intention-to-treat will be performed to test the difference in primary and secondary outcomes between the intervention groups. Student’ s *t* test (parametric continuous data), the Mann-Whitney *U* test (nonparametric continuous data) or the chi-square analysis (categorical data) will be used. A *p* value < 0.05 (two-sided tests) will be taken as threshold of statistical significance.

The observational arm will be analyzed separately, comparing the same treatment groups against the same outcomes using multivariable linear regression to adjust for potential confounders (age, sex, handedness, smoking, fracture type).

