### Recruitment

Patients will be approached on presentation to a participating institution either in the emergency department or in the outpatient setting. Patients aged 70 years and over with a displaced proximal humerus fracture with tuberosity involvement will undergo a computed tomography (CT) scan with 3D reconstructions to assess the fracture configuration and to assess the number of fracture parts according to Neer’s classification [6] (Table 1). Linear measurements will be made with digital calipers. The normal neck shaft angle will be assumed to be 130°. Verbal consent will be requested to allow questioning to assess eligibility and to collect identifiable data. The fracture type will be screened against the inclusion criteria by two of the principal investigators. Patients who satisfy the study criteria will be invited to participate in the study and will receive a Participant Information Sheet (see Additional file 1). Patients who are willing to participate in the randomized trial will be asked to sign a Consent Form. Basic demographic and radiographic data will be collected for both groups to assess independent variables (age, gender, fracture type, diabetes (yes/no), smoking status (current/non), baseline shoulder function (American Shoulder and Elbow Society (ASES) score, Disability of the Arm, Shoulder and Hand (DASH) score) and baseline health (EuroQol Health Survey 5 dimensions (EQ-5D) and EuroQol Visual Analog Scale (EQ-VAS)). Patients who are unwilling to participate in the randomized trial will be offered participation in the observational study and will be provided with a separate Participant Information Sheet and Consent Form.

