### Randomization

Randomization will occur immediately after consent has been gained. Randomization will occur by using a central, telephone-based automated randomization service with each site having its own access code (provided by the NHMRC Clinical Trials Center). Randomization will be stratified by site and will use minimization to adjust for gender and age (70–80 years, over 80 years).

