#### Sample size calculation

Case series documenting the outcome after reverse shoulder arthroplasty have shown a standard deviation (SD) of 13 in the ASES score. The minimum important clinical difference (MICD) in ASES scores has been estimated to be 6.4–18 [28, 32]. We consider a difference of 10 to be necessary in order to justify the additional costs and risks of surgery. A total of 60 patients (30 in each group) will provide 80% power to detect a MICD of 10 points at a significance of 0.05. We aim to recruit 72 patients to allow for 17% loss to follow-up. The ASES score after reverse shoulder arthroplasty has been reported to be 68–86 (higher score being better) [33]. In a paper reporting the outcomes of two-, three- and four-part fractures (our study proposal is limited to three- and four-part fractures) treated nonsurgically the mean ASES score was 82.5 [13].

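### The randomised comparison is fixed as unadjusted although allocation is balanced on site, sex and age and baseline ASES is collected; if these predict outcome, the test is conservative and forgoes precision

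*Protocol article*

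**What the plan says.** All references are to the protocol article.

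- **Statistical analysis** fixes the randomised comparison: "Unadjusted analysis by intention-to-treat will be performed to test the difference in primary and secondary outcomes between the intervention groups". The methods are Student's t test, the Mann-Whitney U test, "or the chi-square analysis (categorical data) will be used". None of these takes covariates. The threshold is "0.05 (two-sided tests) will be taken as threshold of statistical significance". The only covariate-adjusted model in the article is for the observational arm.
- **Randomization**: "Randomization will be stratified by site and will use minimization to adjust for gender and age", with age split into 70–80 and over 80 years. Study design gives eleven centres.
- **Recruitment** lists what is collected at baseline, including "baseline shoulder function (American Shoulder and Elbow Society (ASES) score, Disability of the Arm, Shoulder and Hand (DASH) score", as well as EQ-5D and EQ-VAS.
- **Sample size calculation**: "A total of 60 patients (30 in each group) will provide 80% power", using case series that "have shown a standard deviation (SD) of 13 in the ASES score" and a target difference of 10 points ("We consider a difference of 10 to be necessary").

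The choice is stated, not left open. An analysis plan whose primary analysis was adjusted would depart from this text.

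**The concern.** Stratifying and minimising make sense if the factors are thought to matter for outcome. When they do, the restricted allocation removes most of their contribution from the difference between arms. A two-sample test does not know this: it leaves their variance in the residual SD and so in the standard error. The interval is then wider than the true sampling error warrants, and the test rejects less often than 5% under the null.

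Baseline ASES works differently. Allocation does not balance it, so leaving it out does not distort the size of the test. It only leaves explainable variance in the residual.

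At stake is precision in a trial planned on 60 evaluable patients, using data that will already have been collected.

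**Working it through.** **1. The plan's own figure.** Inputs from Sample size calculation: difference 10, SD 13, 80% power, two-sided 0.05.

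- Normal formula: n per arm = 2 × (1.960 + 0.842)² × 13² / 10² = 26.5, so 27. The exact t calculation gives 28.
- At the planned 30 per arm, SE = 13 × √(2/30) = 3.36. Power is 84.6% (normal) or 83.4% (exact t). The 95% half-width is 2.00 × 3.36 = 6.7 points.

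So 30 per arm meets the stated 80% for the unadjusted test, with a small margin.

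**2. Precision available by formula.** The share of outcome variance explained by the covariates (R²) is not in the documents and is an assumption throughout. The residual SD is 13 × √(1 − R²).

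| Assumed R² | Residual SD | Half-width | Exact-t power, 30 per arm |
|---|---|---|---|
| 0 | 13.0 | 6.7 | 83.4% |
| 0.10 | 12.3 | 6.4 | 87.0% |
| 0.20 | 11.6 | 6.0 | 90.6% |
| 0.30 | 10.9 | 5.6 | 93.8% |

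The power column charges nothing for the extra model terms, so it is an upper guide.

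**3. Simulation under restricted allocation.** Settings: 60 patients, 11 sites, biased-coin minimisation (probability 0.8) on site, sex and age, total SD 13, 3,000 runs per scenario. The biased coin is an assumption. Site enters as fixed terms in the adjusted models.

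| Variance explained: site / sex and age / baseline | t-test type I error | Adjusted type I error (site, sex, age) | Power: t test | Power: site, sex, age | Power: plus baseline |
|---|---|---|---|---|---|
| 0 / 0 / 0 | 5.2% | 4.7% | 83.0% | 78.4% | 77.2% |
| 0.05 / 0.10 / 0 | 3.5% | 4.5% | 84.9% | 84.7% | 84.4% |
| 0.10 / 0.10 / 0.10 | 3.4% | 4.9% | 84.8% | 86.7% | 89.9% |
| 0.10 / 0.20 / 0.20 | 2.6% | 5.2% | 85.9% | 90.9% | 97.0% |

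The third row shows the mechanism. The t test reports a mean SE of 3.33, but the true sampling SD of the difference is 3.08. The effective critical value is 2.00 × 3.33 / 3.08 = 2.16, which on 58 degrees of freedom has a two-sided tail of about 3.5%. That matches the simulated 3.4%.

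**4. Sensitivity to how site is handled.** A separate simulation (60 patients, 11 sites, SD 13) gave the following.

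- Nothing prognostic: t-test size 5.2%. Power goes from 84% to 83% when sex, age and baseline are added, and to 80% with fixed site terms.
- Site, sex/age and baseline each explaining 10%: t-test size 3.2%. Power goes from 85% to 91–92%.

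Taken with step 3, the range from an unadjusted 84% or so is about 83% (nothing prognostic; 77–80% with fixed site terms) to about 90–92% (total R² about 0.3). The last row of the table goes beyond this, but it needs half of the variance to be explained.

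**The case against.** The strongest case against is that nothing here is invalid. The unadjusted test gives an unbiased estimate, any error in size is conservative, and the sample size was computed for that test. All of that stands. A reader might infer that the trial is underpowered or its result unreliable because of this choice; step 1 of the working shows otherwise.

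A reader might also take it as settled that the interval will be too wide and power wasted. The documents do not support that, because they give no figure for how far any factor predicts 24-month ASES. With 5% of variance from site, 10% from sex and age and none from baseline, adjustment gains no power, although it does bring the test size closer to 5%.

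Baseline ASES cannot be assumed to be strongly prognostic. It is collected after the fracture, up to 28 days later under Study population, and the article does not say whether it describes current or recalled pre-injury function. A current score may cluster low and a recalled score high; either would weaken the correlation.

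Finally, it is tempting to call the adjusted observational analysis inconsistent with the unadjusted randomised one. It is not. Treatment is chosen in the observational arm, so adjustment there deals with confounding, which randomisation removes. The reason to adjust the randomised arms is precision and agreement with the allocation scheme.

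Two objections bear on the remedy. Eleven fixed site terms for 60 patients (60/11, about 5 per site) can cost more than they return. ASES is also bounded at 100, and the plan's Mann-Whitney fallback has no direct counterpart in a linear model, which is a reason to keep the unadjusted test in the plan.

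**Conclusion.** The point holds as a conditional improvement in efficiency and in matching the analysis to the design. If site, sex/age and baseline ASES each explain about 10% of the outcome variance, the planned test runs at about 3–4% instead of 5%, and adjustment raises power from about 84% to about 90–92%. If nothing is prognostic, the planned test has the correct size. Adjustment then costs about 1 percentage point of power without site terms, and about 4 to 6 points with 11 fixed site terms (84% to 80%; 83.0% to 77.2%).

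These figures rest on the plan's SD of 13 and difference of 10, on 30 evaluable patients per arm, and on assumed R² values and an assumed minimisation algorithm that the documents do not give. The stated 80% power is unaffected.

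**What to change.** In Statistical analysis, replace the unadjusted primary comparison with an intention-to-treat linear model of 24-month ASES on treatment, sex, age group and baseline ASES. Enter site as a random intercept, or pool small sites, in preference to 11 fixed site terms. Use the matching model, each with its own baseline score, for DASH, EQ-5D and EQ-VAS. Keep the unadjusted test as a pre-specified sensitivity analysis.

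In Recruitment or Randomization, state that baseline scores are recorded before the randomisation call, since randomisation follows consent immediately and participants are not blinded. State also whether baseline ASES refers to pre-injury or current function.

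The cost is wording only, with no extra patients, visits or data items. The downside is about 1 percentage point of power if no covariate is prognostic. That figure comes from the model without site terms; the random intercept was not simulated separately, so its cost should be checked when the model is finalised.

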### Outcome measures

Participants will be followed up at 6 weeks, 3 months, 6 months, 1 year, 2 years, 5 years and 10 years. The outcome measures listed below will be assessed at 6 weeks, 3 months, 6 months, 1 year, 2 years, 5 years and 10 years.

The primary outcome will be the ASES (American Shoulder and Elbow Society) standardized shoulder assessment score patient self-reported section at 24 months [27]. This scoring system consists of two dimensions: pain and activities of daily living, which are both equally weighted giving a total score out of 100, with higher scores indicating less pain and better function. It has been shown to be reliable, valid and responsive in shoulder arthroplasty and fracture [28, 29]. Secondary outcome measures will include DASH (Disability of the Arm, Shoulder and Hand) score [30], the EQ-5D and the EQ-VAS, pain (verbal numerical rating scale, 0–10 points), radiological parameters and complications (repeat shoulder surgery, readmission, infection requiring treatment, neurological deficit, dislocation, death). Radiographs will be performed at each follow-up and will include a four-radiograph series: an AP view in neutral and 30° external rotation, and a transthoracic scapula “Y” view and axillary view. Radiographic parameters that will be assessed are: healing of the tuberosities (nonunion or resorption will be considered failures to heal), position of the tuberosities, scapula notching (according to the Sirveaux classification system [31]) and loosening and alignment (coronal and sagittal plane for patients treated nonoperatively). All radiographs will be assessed by two independent observers independently. In case of discrepancy the scoring will be decided by discussion.

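### The named 24-month two-sample test is a complete-case analysis unless missing scores are handled some other way, and it leaves the earlier ASES scores unused

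*Protocol article*

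**What the plan says.** All references are to the protocol article.

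- **Outcome measures:** the primary outcome is the ASES "standardized shoulder assessment score patient self-reported section at 24 months". The schedule is "The outcome measures listed below will be assessed at 6 weeks, 3 months, 6 months, 1 year, 2 years, 5 years and 10 years", so four post-baseline visits come before the primary time point.
- **Recruitment:** data taken at entry include "baseline shoulder function (American Shoulder and Elbow Society (ASES) score".
- **Sample size calculation:** 60 patients (30 per group) are said to give 80% power for a 10-point difference, with an SD of 13 and a significance level of 0.05. Then: "We aim to recruit 72 patients to allow for 17% loss to follow-up".
- **Statistical analysis:** "Unadjusted analysis by intention-to-treat will be performed to test the difference in primary and secondary outcomes" between the two groups. For continuous outcomes the choice is between Student's "test (parametric continuous data), the Mann-Whitney" test, two-sided at 0.05.

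The article does not define intention-to-treat. It does not say how a missing 24-month score is treated, and it does not say that patients without one are excluded.

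**The concern.** The article fixes a method for the primary analysis: an unadjusted two-sample test at one time point. Such a test takes one score per patient, so a patient with no 24-month score cannot enter it unless a value is supplied first. The sample size paragraph fits this reading, since power rests on 60 patients and the other 12 are recruited only to cover loss.

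Two things are at stake.

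- **Bias.** A complete-case comparison of means is free of bias when loss is unrelated to outcome within each arm, or when the effects of loss happen to cancel between arms. Patients are 70 or older and know their treatment, one arm has surgery and the other does not, and death is a recorded event. Neither condition can be taken for granted.
- **Information.** Many patients lost before 24 months may already have ASES scores from earlier visits. Those scores carry information on the 24-month result and on who is lost, and the named tests use none of it.

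**Working it through.** **1. Inputs from the article.** Difference 10, SD 13, two-sided alpha 0.05, 60 patients for power, 72 recruited, 17% loss. The 24-month time point comes from the study objectives and outcome sections. The abstract gives 12 months; the same reasoning would apply there, with fewer earlier visits.

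**2. The article's own figures.**
- Loss: 1 − 60/72 = 16.7%, stated as 17%, so 12 of 72. In reverse, 60/(1 − 0.17) = 72.3. The loss allowance reproduces.
- Base size: an exact t-test calculation needs 28 per arm for 80% power. Dividing by the Mann-Whitney efficiency of 0.955 gives 28/0.955 = 29.3, rounded up to 30 per arm. The figure of 60 reproduces with that allowance and is slightly conservative for a t test.
- Power with 30 per arm: 83.4% (t test), 81.6% (Mann-Whitney, efficiency 0.955). Both exceed 80%.

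**3. Size of a possible bias (loss rates and gaps are assumed).** In one arm, complete-case mean minus full mean = f × g, where f is the fraction lost and g is how many points lower the lost patients score than those retained.
- Loss of 10% and 24% (17% overall) with g = 15 in both arms: 0.10 × 15 = 1.5 and 0.24 × 15 = 3.6. The net error is 2.1 points, or 21% of the 10-point target.
- Six of 36 lost in each arm, with a gap of d points in one arm only: error = d × 6/36 = d/6. This gives 0.8 points for d = 5, 1.7 for d = 10 and 3.3 for d = 20.
- Equal loss and equal gap in both arms: the error is zero.

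**4. Precision from the earlier scores (correlation r is assumed; the article gives none).** Take 36 randomised per arm, 30 seen at 24 months, every lost patient with one earlier score, and data missing at random. The variance of the 24-month mean in one arm is then

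SD² × [(1 − r²)/30 + r²/36].

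For both arms together this gives effective N = 60/(1 − r²/6).

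| r | Effective N | Power (t) |
|---|---|---|
| 24-month scores only | 60 | 83.4% |
| 0.6 | 60/0.940 = 63.8 | 85.7% |
| 0.7 | 60/0.918 = 65.3 | 86.5% |
| 0.8 | 60/0.893 = 67.2 | 87.4% |

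If only half of the lost patients have an earlier score, 36 becomes 33. Effective N = 1/[(1 − r²)/60 + r²/66], which is 62.0 to 63.7 for r of 0.6 to 0.8, with power 84.6% to 85.6%. Any gain from adjusting for baseline ASES comes on top and is not counted.

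**The case against.** A reader might infer three stronger things, and the article supports none of them.

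- **That the article drops 12 patients.** It nowhere says so. Twelve is an expected number, and exclusion is inferred from the tests named and from the sample size. A two-sample comparison can be run on imputed data, and missing-data handling is commonly left to a full protocol or SAP, neither of which is shown. Its absence is no error. What stands is that the article does name the primary method, and, applied as written, that method uses observed 24-month scores only.
- **That the intention-to-treat label is false.** Comparing patients in the group to which they were randomised meets a common reading of the term, and a complete-case test keeps to it. Only the stricter reading, in which every randomised patient is included, would not be met. The article does not commit to either.
- **That power falls short.** It does not. The 72 recruited already cover the loss.

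The bias figures also have limits. The loss rates and gaps are chosen, and the article gives no evidence that loss will differ by arm. Several features should hold down outcome-related loss: patients must be available for 24 months, aged-care residents and cognitively impaired patients are excluded, and scores are collected by telephone.

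The alternative is not free of assumptions either. A likelihood-based model corrects only the part of the bias that observed scores predict, so the 2.1 points in the working is not its benefit. It also implicitly estimates scores for patients who died. Adding baseline ASES departs from the stated unadjusted analysis, and an unstructured covariance over five visits may be hard to fit with 72 patients.

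**Conclusion.** The point holds as a cheap improvement to a stated method. Unless missing scores are handled in a way the article does not describe, the primary test is a complete-case analysis by randomised group. It ignores the ASES scores from baseline to 12 months and is exposed to bias if loss depends on arm and earlier outcome.

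The gain in precision is modest: from 83.4% power to between 85.7% and 87.4%, if every lost patient has one earlier score correlated 0.6 to 0.8 with the 24-month score and data are missing at random, and less if fewer have one. The stronger reason for the change is protection against bias. Its size cannot be known from the article; under the assumed patterns shown it runs from zero to about 3 points against a 10-point target. The planned 80% power is not in question.

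**What to change.** State as the primary analysis one likelihood-based repeated-measures model of ASES at 6 weeks, 3, 6, 12 and 24 months. Include all randomised patients with any post-baseline score, in their randomised group. Fit treatment-by-visit and baseline-ASES-by-visit terms with an unstructured covariance, and name a simpler structure to use if that does not converge. Take the 24-month treatment contrast as the primary estimate.

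Add a delta-shift sensitivity analysis in which missing 24-month scores are moved by a stated range, separately by arm. Show deaths by arm next to the primary result; death is already a listed complication.

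The cost is a wording change and slightly more analysis work. Every score needed is already scheduled, so patients carry no extra burden. The price is a missing-at-random assumption, which the sensitivity analysis probes, and reliance on the fallback covariance if the sample proves too small for the first choice.

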### Study population

Patients will be considered for the study if they are 70 years of age or older, medically fit for surgery, have a three- or four-part proximal humerus fracture according to Neer’s classification [6] (Table 1), present within 28 days after injury, and are available for follow-up for 24 months.

**Table 1 Tab1:** Neer’s classification of proximal humeral fractures and radiological inclusion criteria

Potential fracture “parts” (Neer)	Head (H), Shaft (S), Lesser tuberosity(LT), Greater tuberosity (GT)
Definition of a “part” (Neer)	>1 cm displacement or >45° rotation. Normal neck shaft angle 130°
Radiological inclusion criteria	3-part fractures: H + GT, S and LT H + LT, S and GT H, LT + GT and S H, GT, LT + S H, LT, GT + S 4-part fractures: H, LT, GT and S

Patients will be excluded if they are unable to provide consent due to limited proficiency in English or cognitive impairment (three or more errors on the Mini Mental Status Examination 6-item screening tool) [26], live in a residential aged care facility, have a pre-existing injury or condition of the affected side which severely affects the movement of the shoulder, a pathological fracture, other injury to the same upper limb requiring surgery, an open fracture, a fracture-dislocation or head-splitting fracture, a glenoid fracture, gross fracture displacement (no bony contact between humeral shaft and articular segment) or an axillary nerve palsy.

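### Complications and death are followed to 10 years, but the only test named that fits them is chi-square, which cannot use time at risk or censored follow-up; late proportions are misstated if patients are lost

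*Protocol article*

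**What the plan says.** All references are to the protocol article.

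- **Study population.** Entry is limited by age: "Patients will be considered for the study if they are 70 years of age or older".
- **Outcome measures, schedule.** "The outcome measures listed below will be assessed at 6 weeks, 3 months, 6 months, 1 year, 2 years, 5 years and 10 years".
- **Outcome measures, events.** The secondary outcomes include "complications (repeat shoulder surgery, readmission, infection requiring treatment, neurological deficit, dislocation, death". No time-to-event definition is given.
- **Outcome measures, primary.** The primary outcome is the ASES "standardized shoulder assessment score patient self-reported section at 24 months".
- **Statistical analysis.** "Unadjusted analysis by intention-to-treat will be performed to test the difference in primary and secondary outcomes between the intervention groups". The tests are then assigned by data type: a t test or Mann-Whitney test for continuous data, and for the rest, "or the chi-square analysis (categorical data) will be used". No method for event times, censoring or competing events is named for any outcome.
- **Sample size calculation.** The only allowance for loss is here: "We aim to recruit 72 patients to allow for 17% loss to follow-up". It is tied to no visit.

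**The concern.** Repeat surgery, infection, dislocation, readmission and death build up over time. A chi-square table asks for a single status per patient at a single time. A patient last seen event-free at year 3 has no known status at year 10, so the table must either count that patient as event-free or leave the patient out. The first choice makes the proportion too low and the second makes it too high. If loss differs between arms, part of the difference in loss appears as a difference in complications.

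At stake is the long-term safety comparison. The Background section reports a high complication rate for the implant, and follow-up runs to five times the length of the primary endpoint. With about 36 patients per arm, a few misclassified patients change the reported risk visibly.

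**Working it through.** **What the documents supply.** 72 recruited, so 36 per arm; 17% loss; visits at 2, 5 and 10 years. The loss figure agrees with the sample size to rounding: 1 − 60/72 = 16.7%. There is no stated complication, death or late-loss rate to reproduce, so every rate below other than the 17% is an assumption. Treating the 17% as a constant rate per 2 years is also an assumption.

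**Model.** Constant yearly hazards: *h* for a first complication, *d* for death, *l* for loss, independent of each other.

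- True cumulative incidence by time *t*: h/(h+d) × [1 − exp(−(h+d)t)]
- Observed events over randomised, lost counted as event-free: h/(h+d+l) × [1 − exp(−(h+d+l)t)]

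With *l* = 0 the two expressions are identical. Death alone therefore introduces no error when the dead are kept in the denominator.

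**Case A: 17% loss per 2 years, 20% complication risk at 10 years without death.**

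- l = −ln(0.83)/2 = 0.0932; h = −ln(0.80)/10 = 0.0223.
- Not lost, before any deaths: 36 × exp(−0.0932 × 5) = 22.6 at 5 years; 36 × exp(−0.0932 × 10) = 14.2 at 10 years.
- With d = 0, at 10 years: true 20.0%, observed 13.2%, a relative shortfall of 34%.
- With d = 0.05, by choice of denominator:

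| | 2 years | 10 years |
|---|---|---|
| True cumulative incidence | 4.2% | 15.9% |
| Lost counted as event-free | 3.8% | 10.9% |
| Event-free lost dropped | 4.5% | 20.0% |
| Event-free lost and dead dropped | 5.0% | 36.3% |

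The last two rows at 10 years follow from the probability of being lost event-free, 0.455, and of still being alive, event-free and followed, 0.191: 0.109/(1 − 0.455) = 20.0% and 0.109/(0.109 + 0.191) = 36.3%. The relative shortfall in the second row is 31% at 10 years and 9% at 2 years, from unrounded values.

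**Case B: lighter loss.** h = 0.03; d = 0.04, 0.07 or 0.10; l = 0.03 or 0.06. With lost patients counted as event-free, the relative shortfall is 3–6% at 2 years, 6–13% at 5 years and 11–22% at 10 years. For example, with d = 0.07 and l = 0.03, 16.8% is observed against a true 19.0% at 10 years.

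**Unequal loss, equal true risk.** With the Case A event hazard, d = 0.05, and loss of 10% against 24% per 2 years (l = 0.0527 and 0.1372), the arms show 12.7% and 9.3% at 10 years. Both true values are 15.9%. In patients, that is 4.6 against 3.4 of 36.

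**Effect on the test.** In 20,000 simulated trials of 36 per arm (h = 0.03, d = 0.07, lost counted as event-free, no treatment effect), chi-square rejects at 10 years in 5.3% with equal loss of 3% a year. It rejects in 6.7% with loss of 1% against 6% a year.

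**Censoring deaths is not the remedy.** With h = 0.03, one minus Kaplan-Meier with deaths censored gives 1 − exp(−0.3) = 25.9% at 10 years, against a true cumulative incidence of 16.8–21.6% for d from 0.10 to 0.04.

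**The case against.** **The article ties chi-square to no visit.** The Statistical analysis section assigns tests by data type, and the 5- and 10-year visits appear in an assessment schedule. A reader might infer that chi-square is prescribed at every visit; the text does not say so. What remains is that the test is stated for secondary outcomes generally, these outcomes are scheduled to 10 years, and no other named method could apply.

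**Denominators and lost patients belong in a fuller document.** That is fair, and their absence is not the point here. The point is the method the article does name, which cannot use censored follow-up whatever denominator is later chosen.

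**Death as a competing event does not make a crude proportion wrong.** This stands in full. The gap between 15.9% and 10.9% comes from loss. Death matters only if the dead are dropped, or if mortality differs by arm, when a difference in cumulative incidence cannot separate fewer complications from fewer survivors. Death is also itself on the complications list, so in an analysis of all listed events together it counts as an event.

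**The background does not make late implant failure the main risk.** This also stands. It lists several complications without ranking them and ties prosthetic longevity to limited use in young patients, who are not this population.

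**The sizes rest on assumed rates, and the effect on the test is small.** Correct. The distorted comparison above amounts to about one patient, and false-positive rates stay between 5% and 7%. The greater harm is to the reported late risks.

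**Conclusion.** The point holds in a conditional form. The only test named that fits complications and death cannot use time at risk or censored follow-up, and these outcomes run to 10 years in patients aged 70 or over. If follow-up is incomplete, counting lost patients as event-free understates the proportion by about 11–34% in relative terms at 10 years and 3–9% at 2 years. That range covers assumed loss from 3% a year up to 17% per 2 years, with constant and independent hazards. Dropping lost or dead patients overstates it, and unequal loss distorts the comparison.

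A reader might go further and conclude that late complication rates will be wrong in any event. The documents do not support that: they give no late loss, and with complete status the crude proportion is correct. The issue is confined to late secondary outcomes and leaves the 24-month ASES comparison untouched. It is a cheap improvement.

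**What to change.** Record the date of each complication and death, and the date each patient was last known event-free. For complications at 5 and 10 years, and at 2 years if loss is material, report Aalen-Johansen cumulative incidence by arm. Treat death as a competing event for non-fatal complications and loss as censoring, and give the between-arm difference with a 95% confidence interval. Analyse death by Kaplan-Meier and log-rank. Keep chi-square for early visits where follow-up is near complete.

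The cost is one or two sentences of analysis text, date fields on the event form and slightly more analysis work; no patients or visits are added. The method assumes that loss is non-informative, which should be stated. The date fields are best added early, since dates are hard to recover years later.
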